## Abstract

**Background:**

Non-didactically delivered curriculum based group psychoeducation has been shown to be more effective than both group support in a specialist mood disorder centre in Spain (with effects lasting up to five years), and treatment as usual in Australia. It is unclear whether the specific content and form of group psychoeducation is effective or the chance to meet and work collaboratively with other peers. The main objective of this trial is to determine whether curriculum based group psychoeducation is more clinically and cost effective than unstructured peer group support.

**Methods/design:**

Single blind two centre cluster randomised controlled trial of 21 sessions group psychoeducation versus 21 sessions group peer support in adults with bipolar 1 or 2 disorder, not in current episode but relapsed in the previous two years. Individual randomisation is to either group at each site. The groups are carefully matched for the number and type of therapists, length and frequency of the interventions and overall aim of the groups but differ in content and style of delivery. The primary outcome is time to next bipolar episode with measures of the therapeutic process, barriers and drivers to the effective delivery of the interventions and economic analysis. Follow up is for 96 weeks after randomisation.

**Discussion:**

The trial has features of both an efficacy and an effectiveness trial design. For generalisability in England it is set in routine public mental health practice with a high degree of expert patient involvement.

**Trial Registration:**

ISRCTN62761948

## Background

Recurrence rates for mania and depression in bipolar disorder are high; around 50% at one year and 70% at four years [1,2]. Group psychoeducation in addition to maintenance medication is recommended by most recent bipolar disorder practice guidelines for the maintenance management of bipolar disorder [3-6]. In Barcelona, two randomised controlled trials showed that structured curriculum based group psychoeducation for up to 21 sessions increased time to relapse in all types of bipolar episode in patients who were concordant or not concordant with mood stabiliser medication compared to non-didactic group support not following a curriculum [7,8]. The gains were maintained over the next five years with marked reductions in hospitalisation and improvements in function [9]. Subgroup analysis showed improvements with psychoeducation versus control intervention in bipolar 2 disorder [10] and in bipolar disorder with or without personality disorder [11]. In Australia, two randomised controlled trials showed that 12 sessions of non-didactic curriculum based group psychoeducation reduced the rate of bipolar episode relapse compared to treatment as usual [12,13].

The trials in Barcelona were conducted in a specialist bipolar disorder service and the nature of the group support provided in the trials was not well characterised. In the United Kingdom, lay led peer support groups led by service users are more frequently found than in other European countries [14]. Although, generally peer support groups may improve self-efficacy and may be cost effective [15] their effectiveness in bipolar disorder is less certain. However, self management strategies to stay well, (developed by service users with bipolar disorder who had no bipolar episodes for at least two years) were valued as important as medication [16]. Therefore a pragmatic randomised controlled trial is needed to compare group psychoeducation close in format to the Barcelona programme with peer group support where patients identify their own learning needs. Such a trial would tease out whether the content of the Barcelona psychoeducation programme is more or less effective than the group process of bringing together people with bipolar disorder facilitated by health professionals.

The trial also permits further work to be conducted on the mechanisms of action of group psychoeducation. The Barcelona model of psychoeducation incorporates all of the recommended components of psychological treatment recommended by NICE [3] such as early warning signs [17], medication adherence [18], and maintaining a regular daily routine [19] together with psychoeducation about the disorder, and medication. Importantly the groups use the collective experiences of the group members to bring about positive changes in attitudes, knowledge and behaviour among the participants.

## Methods/Design

### Objective

To determine the clinical and cost effectiveness of joint expert patient and health professional led group psychoeducation for bipolar disorder versus unstructured peer group support.

Main research questions:

• To demonstrate that group psychoeducation is feasible and sustainable across different non-specialist sites across the English National Health Service

• To determine the clinical and cost effectiveness of group psychoeducation compared to peer group support

• To identify barriers and potential solutions to barriers to the implementation of effective group psychoeducation

### Design

A randomised controlled trial compares the effectiveness of:

• 21 weekly session bipolar group psychoeducation, delivered by two health professionals (nurse, psychiatrist, psychologist, occupational therapist) and an expert patient, plus treatment as usual from the psychiatrist and other health professionals versus

• 21 weekly session unstructured bipolar group support, led by peers and facilitated by two health professionals and the expert patient, plus treatment as usual for patients with bipolar disorder (Figure 1).

**Figure 1 F1:**
[figure not shown]
**Design of the study**.

The trial is located in two centres (East Midlands and North West) in England, with four clinical sites in each centre. There are five waves so that the largest clinical sites run two groups each and the remaining clinical sites run one group each. The intervention is taken to different parts of a regional centre to improve access for those people wish to participate but for whom travelling distance is a practical barrier to engagement.

Consecutively eligible patients are individually randomised to either intervention with stratification by clinical site and minimisation in terms of number of previous bipolar episodes (<7, 8-19, 20+) (see Figure 1). The latter is to control for the effect of rate of bipolar episodes: relapse is up to three times greater in those with more than 20 episodes than in those with less than seven bipolar episodes [20]. In some RCTs of psychosocial interventions in bipolar disorder there may be an interaction between psychological treatment and number of previous bipolar episodes [21]. Barriers to the effectiveness of either intervention are examined qualitatively by interviewing maximum variance samples of participants and group facilitators.

### Setting

Community mental health team bases at a number of NHS Trusts located in two distinct geographical centres (East Midlands and North West) are used to ensure the generalisability of the findings. The study is also promoted at a primary care level with local family doctors being asked to display posters about the trial. Research assistants (RAs), service user researchers and community scientific officers from the Mental Health Research Network in England visit support groups such as the Manic Depression Fellowship (MDF), Poles Apart and Mood Swings to introduce the study and provide referral information.

### Target population

The target population is patients with bipolar 1 or 2 affective disorder at increased risk of further relapse (an episode in the last 24 months). In clinical practice patients at increased risk of further relapse are the targets for interventions aimed at preventing further relapse rather than patients who have been stable for several years.

### Inclusion/exclusion criteria

Inclusion criteria are:

• a SCID-DSM-IV verified diagnosis of primary bipolar disorder [22],

• at increased risk of relapse (at least one episode in the last 24 months),

• age 18 years or more.

Exclusion criteria are:

• presence of a current manic, hypomanic, mixed affective or major depressive episode currently or within the previous four weeks,

• current suicide plans or high suicide intent,

• inability or unwillingness to give written informed consent to the study.

• inability to communicate in written and verbal English to a sufficient level to allow them to complete the measures and take part in the groups.

### Baseline and Outcome Measures

At baseline interview the Structured Clinical Interview for DSM-IV (SCID) is used to assess sociodemographic features, the presence of axis 1 comorbid psychopathology [23], the presence of borderline or antisocial personality disorder [24] and the number of previous bipolar episodes. Participants are also asked at baseline how effective they think each of the two treatments is likely to be and if they have any preference as to which group they are allocated to.

The primary outcome measure is:

• time to next bipolar episode, average weekly symptom score (both established using 16-weekly SCID Longitudinal Interval Follow-up Evaluation (LIFE) interviews [25,26] to generate weekly scores of mania and depression on 1-6 scale of severity), as we have previously used [20,21].

Secondary outcome measures include:

• time to next manic-type episode (mania, hypomania or mixed affective episode) and time to next depressive episode [20,21]

• assessment of mean and variability in weekly symptoms of mania type symptoms and depression symptoms using the LIFE [20,21]

• assessment of function using the Social Adjustment Scale [27] and SOFAS [28];

• observer and self-rated measures of mood: 17 item Hamilton-GRID (HDRS) [29,30]; Bech-Raphaelson Mania Scale (MAS) [31]; Hospital Anxiety & Depression Scale (HAD) [32];

• medication adherence (Medad) [33];

• health status and related utility values using the Euroqol 5D [34,35] and health and social care costs from a broadly societal perspective.

Further measures are used to explore the process of change with treatment:

• The Hayward Stigma Questionnaire [36], an eight-item self-report questionnaire to examine if effectiveness of the groups might be related to reductions in stigma.

• The KAB (Knowledge about Bipolar Disorder). This is based on the Knowledge About Schizophrenia Inventory [37], and asks questions on knowledge about bipolar disorder found in the group psychoeducation manual. The questions were tested on groups of service users with bipolar disorder before the trial to ensure that the questions were understood and that the KAB did not have either ceiling or floor effects. The questionnaire is used to determine if differences in outcome between the two groups might be due to differences in the knowledge of bipolar disorder acquired by the participants.

• The Hypomania Interpretations Questionnaire [38], a 10-item self-report questionnaire to explore if either group changed positive self-dispositional appraisals for hypomania-related experiences.

• The Social Rhythm Metric [39,40] trait and diary forms are completed over one week. The habitual timing of 17 daily behaviours is assessed.providing information on the number, timing and frequency of occurrence of regular activities.

• The Short-Form 12 (SF-12) [41], a 12-item self-completed questionnaire evaluating eight domains of overall health (general health, role physical, physical function, bodily pain, vitality, social functioning, role emotional, and mental health) in the preceding four weeks summarised as physical component scores and mental component scores.

• The Early Warning Signs checklist [42], a 32-item and 31-item checklist of common early warning signs of depression and mania, and the timing of these signs in relation to the onset of a depressive or mania episode respectively.

• The Coping Strategies Checklist [20], a list of adaptive and maladaptive coping strategies employed with the onset of manic symptoms (40 items) [43] and depression (40 items) symptoms. The coping with depression checklist was derived from items from the Response Style Questionnaire [44], the Depression Coping Checklist [45], items from the coping with mania questionnaire [43] that were also relevant to depression according to a panel of service users from a UK service user organisation (the Bipolar Organisation: the Manic Depression Fellowship) plus four additional items suggested by these service users.

• The Brief Illness Perception Questionnaire [20,46], a 11-item self-report measure of beliefs about mood swings in bipolar disorder, each measure on a five point scale of strength of conviction.

In addition, weekly ratings of treatment fidelity for each treatment session during the 21 session treatment are taken using a short checklist designed specifically for this study. Participants are asked to provide feedback specifically on group cohesion [47] and group working alliance (WAI-S) [48] which are administered at weeks 3, 10 and 21 of follow-up.

Follow-up of each patient is for 96 weeks from randomisation. Patients who had not relapsed at 96 weeks are censored on the time to next bipolar episode outcome. SCID-LIFE interviews to collect time to next relapse are collected every 16 weeks alternating between telephone and face to face interview up to 96 weeks.

Face to face assessments are performed at baseline, 32, 64 and 96 weeks after randomisation. Telephone assessment is used for interviews at 16, 48 and 80 week assessments. At 16, 48 and 80 weeks, self-rated questionnaires are e-mailed or posted using reply paid envelopes as the participant requests. Table 1 shows the schedule of assessment. The assessments by telephone have shown to be valid compared to face to face assessment [49,50]. Some of our measures have not been tested psychometrically by telephone compared to face to face assessment so they are delivered face to face. Face to face assessment is performed if telephone assessment is not feasible. We use case notes and interview key workers to determine time to recurrence if patient consents but drops out from direct follow-up [21,51]; a recurrence is defined as a clinically important change in mental state towards either mania or depression resulting in a substantial change in function and/or necessitating change in treatment or management such as change in medication, urgent care or admission to hospital.

**Table 1 T1:** Measures in the study

Every 16 weeks (up to 96 weeks)	Every 32 weeks (up to 96 weeks)
SCID - LIFE at interview	SAS at interview
HDRS at interview	EuroQol at interview
MAS at interview	Economic Interview (CSRI)
SOFAS at interview	SRMetric - trait at interview
MedAd at interview	SRMetric - diary by post
	HADS version 1 by post
	KAB by post
	EWS checklist by post
	Coping strategies checklist by post
	BIPQ by post
	HIQ by post
	Hayward Stigma Questionnaire by post
	SF-12 by post

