### Sample size

When patients receive treatment in groups, interactions between patients may lead to correlation of outcomes of patients in the same group [52] sometimes referred to as cluster. As with cluster randomised trials, sample size calculation needs to consider the possibility of intra-cluster correlation [53]. As there are no previous trials of group interventions for bipolar disorder that have considered clustering, we considered empirical evidence regarding the magnitude of clustering from cluster randomised trials. A previous trial [54] found a negligible clustering effect (0.0001) but this was from a small sample, and so would be imprecisely estimated. We have therefore assumed a small but not zero clustering effect equal to 0.05. Based on the outcomes from the two previous Barcelona protocol psychoeducation randomised controlled trials [7,8] a differential treatment effect of 0.22 was used (60% recurrence in the control group, 38% in the psychoeducation group). Power for 80% probability of detecting a difference at 0.05 level, 2-tailed testing requires 82 patients per arm. Assuming a mean group size of 18 and an intra-cluster correlation coefficient of 0.05, a design effect of 1.85 gives a sample size of 152 in each arm. We have assumed 15% loss to follow up [54] giving a total sample size of 179 per arm (358 in total). This is achieved by running 10 groups of 18 subjects in each arm (10 in the North West and 10 in the East Midlands) over 3 years. Initially 17-18 patents are recruited per group but with attrition there will be 13-14 patients per group, the ideal size for group psychoeducation based on 10 years experience [55].

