### Analysis

Intention to treat using Kaplan-Meier recurrence-free curves with significance tests will be based on the Cox proportional hazards regression model. The level of dependence or heterogeneity among patterns of recurrence

within the same team was estimated by the intracluster correlation coefficient (ICC) using estimate of frailty from the shared frailty model [60]. Trial centre, and number of previous episodes of bipolar disorder, will be included as covariates. Analysis of quantitative secondary outcome measures will use linear mixed models including baseline covariates and random effects for therapy group [52]. The treatment effect may differ according to illness duration/number of episodes with a lesser treatment effect in patients with longer illness duration/more episodes based on findings of the MRC CBT trial [21]. This will be tested in a secondary analysis by adding a severity-treatment interaction into the above models.

The economic analysis will be adjusted for baseline covariates shown to be important predictors of future costs and outcomes (e.g. costs and service use prior to entry, health status and utility, clinical severity and duration of illness, socio-economic status). Bootstrap simulations will be used to estimate cost effectiveness acceptability, net benefit statistics and the likelihood that group psycho-education is cost effective compared to group support. Probabilistic simulation models will be used to explore the generalisability of the results to the UK.

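### The primary Cox model omits mood symptom level at entry; pre-specifying baseline HDRS and MAS as covariates would be a low-cost and probably modest gain in power

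*Protocol article*

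**What the plan says.** Under Analysis, the protocol article tests the primary outcome, time to next bipolar episode, with a Cox model and estimates clustering from a shared frailty model. The covariates are stated: "Trial centre, and number of previous episodes of bipolar disorder, will be included as covariates". No measure of current mood is among them.

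Under Baseline and Outcome Measures, the secondary outcomes include "observer and self-rated measures of mood: 17 item Hamilton-GRID (HDRS) [29,30]; Bech-Raphaelson Mania Scale (MAS) [31]". The primary event comes from a different instrument, the LIFE interview, which gives weekly mania and depression ratings from 1 to 6.

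Under Inclusion/exclusion criteria, mood at entry is restricted only by excluding "presence of a current manic, hypomanic, mixed affective or major depressive episode currently or within the previous four weeks". There is no upper limit on HDRS or MAS.

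Allocation (Design; Randomisation and treatment allocation) is balanced on clinical site and banded number of past episodes, not on current symptoms. The economic analysis is to adjust for predictors of costs and outcomes, with examples that include "costs and service use prior to entry, health status and utility, clinical severity and duration of illness".

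**The concern.** A patient can enter with no symptoms or with symptoms just short of an episode. The primary event is the onset of an episode, so where the patient starts plausibly affects how soon it comes. Number of past episodes describes lifetime history and need not capture current state.

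Omitting a prognostic covariate from a Cox model has two consequences. The hazard ratio averaged over that covariate lies nearer to 1 than the ratio conditional on it, which costs some power. Also, any chance difference between arms in entry symptoms stays in the estimate. The article's Discussion itself warns that uncertain clustering and difficult recruitment may affect the sample size needed, so an inexpensive gain in power is worth having.

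**Working it through.** **Inputs from the Sample size section.**
- Risks: "60% recurrence in the control group, 38% in the psychoeducation group".
- Test: two-sided 5% level with 80% power, for which the article gives 82 per arm before any inflation.
- Clustering: groups averaging 18 members and an ICC of 0.05 are taken, after which "a design effect of 1.85 gives a sample size of 152 in each arm".
- Attrition: 15%, which takes the figure to 179 per arm, or 358 overall.

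**Assumed input.** The hazard ratio per SD of entry symptoms is not in the documents. It is varied from 1.0 to 2.0.

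**Step 1: reproduce the plan's figures.**
- Two proportions, pooled variance: n = [1.96·√(2·0.49·0.51) + 0.8416·√(0.60·0.40 + 0.38·0.62)]² / 0.22² = 79.9, so 80 per arm. The stated 82 is within two patients, and power at 82 per arm is 81.0%.
- Design effect: 1 + (18 − 1)·0.05 = 1.85. Then 82·1.85 = 151.7, so 152; 152/0.85 = 178.8, so 179; 2·179 = 358.
- Implied hazard ratio: ln(0.62)/ln(0.40) = 0.522.

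The sample size reproduces, and the present point does not touch it.

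**Step 2: power without and with the covariate.** Simulated trials had 82 independent patients per arm (152/1.85), exponential times and one standard normal covariate. The marginal risks were held at 60% and 38%, with censoring only at the end of follow-up. There were 4,000 runs per row, each analysed by a Cox Wald test with and without the covariate.

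| Assumed HR per SD | Power without | Power with | Gain (points) | Mean log HR without / with | Mean SE without / with |
|---|---|---|---|---|---|
| 1.0 | 81.9% | 82.0% | 0.1 | −0.654 / −0.656 | 0.231 / 0.232 |
| 1.2 | 82.6% | 83.0% | 0.4 | −0.659 / −0.668 | 0.231 / 0.232 |
| 1.35 | 82.1% | 84.6% | 2.5 | −0.657 / −0.677 | 0.231 / 0.232 |
| 1.5 | 83.2% | 86.1% | 2.9 | −0.666 / −0.702 | 0.231 / 0.233 |
| 2.0 | 84.2% | 92.4% | 8.2 | −0.674 / −0.775 | 0.231 / 0.234 |

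The Monte Carlo standard error of one power figure is about √(0.83·0.17/4000) = 0.6 points. Both models were fitted to the same data sets, so the differences are firmer than that. A separate set of 3,000 runs per setting gave 82.9% against 84.6% at 1.3, 83.1% against 86.4% at 1.5, and 82.2% against 87.9% at 1.7.

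The standard error does not fall with adjustment. The log hazard ratio moves away from zero.

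**Step 3: chance imbalance.** With 152 per arm, the between-arm difference in mean entry score has SD √(2/152) = 0.115 of a patient-level SD. At the edge of its 95% range this is 1.96·0.115 = 0.225 SD. At an assumed hazard ratio of 1.5 per SD, the treatment log hazard ratio shifts by roughly 0.225·ln(1.5) = 0.091, a factor of 1.095. An unadjusted ratio of 0.522 would then read between about 0.48 and 0.57.

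**Step 4: cost in degrees of freedom.** Expected events among 152 per arm are 152·(0.60 + 0.38) = 149, against two added terms.

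**Step 5: are the scores available?** Table 1 lists HDRS and MAS every 16 weeks and has no baseline column. It likewise lists EuroQol only under every 32 weeks, yet the Economic evaluation section says EuroQol is completed at baseline. The absence of a baseline column therefore does not mean absence at baseline. The article also describes a face-to-face baseline assessment. A baseline rating is well implied but not stated by name.

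**The case against.** The strongest reply is that the plan's choice is reasoned. It adjusts for a minimisation factor backed by an up to threefold difference in relapse, and for centre. Under randomisation the less adjusted test is valid, and chance imbalance is already allowed for in its error rate. All of that stands.

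The size of the gain is also open to challenge. It rests on an assumed prognostic strength. The simulation omits number of past episodes, which may carry part of the same information. Excluding episodes within four weeks narrows the spread of entry scores. Allocation waits until 20 participants are identified, so a score could be out of date by randomisation. These points make the tabulated gains likely upper values.

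It may be said that covariate lists belong in an analysis plan that is not shown. A fuller list may exist there, but the article states the covariates for this model, so the point addresses a stated choice.

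Three stronger readings are tempting and fail:
- A reader might infer that HDRS and MAS share the outcome's scale. They are separate instruments measuring a related construct; the outcome uses LIFE ratings.
- A reader might infer that precision is lost. The standard error is 0.231 without and 0.232 to 0.234 with the covariate.
- A reader might infer an inconsistency with the economic analysis. That list gives examples for a different endpoint and does not define clinical severity as HDRS or MAS. Elsewhere in the same section, severity refers to illness duration or number of episodes.

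**Conclusion.** The point holds as an optional efficiency improvement. The stated primary model leaves out a plausible prognostic factor that appears to be collected already. Nothing in the documents shows an error, a biased test, a contradiction or a wrong sample size.

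Up to an assumed hazard ratio of 1.5 per SD the power gain is at most about 3 points; only a strong association, such as 2.0, brings it to about 8. Chance imbalance could move the estimate by up to about 10% at 1.5, and adjustment would remove that. The conclusion assumes that both scores are rated at baseline and are prognostic beyond number of past episodes. If they are not prognostic, power is essentially unchanged.

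**What to change.** Confirm that HDRS and MAS are rated at baseline, and say so in the assessment schedule. Then pre-specify the two baseline totals as continuous covariates in the primary Cox/shared frailty model, beside centre and number of past episodes. Use the same two terms in the models for time to manic-type and to depressive episode.

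Report the primary model without them as a sensitivity analysis. State in advance that its hazard ratio is expected to lie slightly nearer to 1 when the scores are prognostic, so that a small gap is not read as evidence of imbalance.

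The cost is analysis-plan wording and two degrees of freedom against about 149 expected events. If the baseline ratings are confirmed, no new data are needed. The change should be fixed before outcome data by arm are seen.
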